### Data management and analysis

#### Data management

Outcomes and other measures will be assessed with patient questionnaires and cognitive assessment, with medical examination and somatic assessment (see Fig. 2) or will be extracted from the rehabilitation discharge letters (e.g. primary and demographic data; socio-medical parameters e.g. employment, current sickness absence, sick leave duration in weeks, ability to work on admission and discharge). For participants who do not complete follow-up questionnaires, missing data will be imputed. If participants withdraw their participation, the collected data will be deleted. The patient data are stored anonymously in a electronic study-data file with a patient cipher, whereby the paper–pencil data are entered manually. Paper-pencil questionnaires will be stored in locked filing cabinets and electronic data will be stored on secured servers. To assure a safe and secure environment for data acquired, data transmission is encrypted with secure socket layer (SSL) technology.

**Fig. 2 Fig2:**
[figure not shown]
Study procedure

#### Statistical methods

Statistical analyses will be conducted using R version 4.0.5 [38], the package lavaan [39], Matlab [40], and/or SPSS 21 or 28 [41] for Windows.

#### Descriptive

Descriptive and explorative analyses will be performed concerning demographic, disease-specific (diagnosis; neurological, cognitive or/and psychological functional impairments) and other factors (e.g. work related factors like ability to work on admission, duration of sick-leave).

#### Treatment effect

Differences in the change scores between the intervention groups (reha-clinics) and the control group (post-COVID ambulance) on the primary (self-report questionnaires, screening dementia, cognitive assessment, somatic assessment) and secondary outcomes (socio medical parameters) will be analysed with multilevel (mixed-model) linear regression analyses taking all three measurements into account (admission, discharge, catamnesis). We will use a model with a random intercept and random slopes will be tested, to see which model fits best. *P* values < 0.05 are considered statistically significant. Differences in the change scores between the intervention groups and the control group on the primary, secondary and other study parameters will be analysed with multilevel (mixed-model) linear regression analyses, taking all three measurements into account. We will perform subgroup analyses for severity, duration and number of the symptoms and comorbidity to explore which patients are most likely to benefit from the intervention.

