**Methods/design:**

As first objective, pulmonal, cardiac, neurological, cognitive or/and psychological functional impairments in rehabilitation patients after COVID-19 disease will be described. The second objective is the differentiated review of the specific rehabilitation measures, in the short term and in the longer term for the purpose of future prognoses and optimisation of therapeutic interventions. This prospective, non-randomised, controlled longitudinal study, plus multi-group comparisons will take place in seven rehabilitation clinics of different specialisations: cardiological rehab, pneumological rehab, neurological rehab, psychosomatic rehab. Within 12 months, 1000 cases across all participating centres will be included. Somatic and psychological testing will be conducted at three measurement points: Admission (t0), discharge (t1), 6-montas Catamnesis (t2). The patients receive the usual care according to the respective rehabilitation priorities, adapted to the special challenges of post-COVID symptoms. Patients of the post-COVID outpatient clinic without rehabilitation will be used as a control group.

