#### Eligibility criteria

SARS-CoV-2-infection and following post-COVID syndrome: Complaints that are still present more than 12 weeks after the onset of SARS-CoV-2 infection and cannot be explained otherwise.As a consequence of the post-COVID syndrome, at the time of the start of rehabilitation, the presence of functional limitations that may threaten the ability to work.Written informed consent to participate in the study.Aged 18 years or above.Sufficient knowledge of the German language to participate in the study.

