### Control group (post-COVID outpatient clinic Regensburg)

This is a matched control group or comparative data from Regensburg Post-COVID Outpatient Clinic. The patients in the Regensburg post-COVID outpatient clinic meet the same inclusion criteria as the study cohorts of the rehabilitation clinics and receive the same diagnostic examinations. Due to the ambulance setting, which focusses only on the diagnostic process, there is no intervention.

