### Strength and limitations

Following the recommendation of the research agenda for post-COVID fatigue [13], this study uses largely internationally established and previously validated instruments to measure fatigue and other post-COVID symptoms. The strengths of this study include the large sample size and the nationwide distribution of the cooperating rehabilitation centres, which thus also reflects regional differences and characteristics of the various rehabilitation indications. The inclusion of different therapy focuses per indication with different intensity and duration of treatment is on the one hand a weakness of the study, as no uniformly defined intervention can be depicted, but on the other hand it reflects the reality of healthcare. This improves the external validity of our study results. The resulting comparison between the different care structures also enables care research to be conducted within this study. We assume that within the framework of this observational study, statements can be made reliably about which and how much therapy the respective patient groups need. With this approach, the treatment of the control group resembles usual care and offers the possibility to make statements about whether pure post-COVID diagnostics might be sufficient for certain patient groups.

However, external validity outside Germany will be limited due to differences in health care systems. A further relevant weakness is that there is no RCT design, but this is difficult for ethical and legal reasons, first because in Germany everyone has a legal right to rehabilitation (entitlement to rehabilitation) and second because rehabilitation is relevant to clarify the socio-medical situation.

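### Matching of the outpatient controls is left optional and the comparison with rehabilitation names no adjustment, yet the article claims to test effectiveness and to support reliable statements on therapy need

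*Protocol article*

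**What the plan says.** The abstract describes the design: "This prospective, non-randomised, controlled longitudinal study, plus multi-group comparisons will take place in seven rehabilitation clinics". It gives one sample-size figure, "Within 12 months, 1000 cases across all participating centres will be included", and defines the comparison group: "Patients of the post-COVID outpatient clinic without rehabilitation will be used as a control group".

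The control-group section says: "This is a matched control group or comparative data from Regensburg Post-COVID Outpatient Clinic". It adds that these patients "meet the same inclusion criteria as the study cohorts of the rehabilitation clinics and receive the same diagnostic examinations", and that they receive no intervention because the outpatient setting is diagnostic only. One of the eligibility criteria is "at the time of the start of rehabilitation, the presence of functional limitations that may threaten the ability to work".

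Under Treatment effect, the plan is to compare "Differences in the change scores between the intervention groups (reha-clinics) and the control group (post-COVID ambulance", using multilevel linear regression over admission, discharge and catamnesis, with a random intercept and possibly random slopes. No covariate, matching variable or weight is named there. Severity, duration and number of symptoms and comorbidity enter only as subgroup variables.

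The Background says that the study tests whether rehabilitation is effective and safe. Strength and limitations concedes the lack of a randomised design as a weakness, but assumes that "statements can be made reliably about which and how much therapy the respective patient groups need", and that the control group can show whether diagnostics alone might suffice for some patients.

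**The concern.** Matched controls and unmatched comparative data are two different designs, and the text permits either. Under the second, nothing in the article separates the effect of rehabilitation from the reasons why a patient was admitted to rehabilitation. The rehabilitation cohort consists of consecutive admissions, routed by symptom focus. The control cohort consists of people who attended a diagnostic clinic and are not in rehabilitation. The two may differ in stage of illness, severity and work situation, and so in their expected course over the following months.

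The statement that both groups meet the same criteria would be some reassurance, but one criterion is dated to the start of rehabilitation, and it is the one that concerns functional limitation and work ability. The model's first two time points have the same problem.

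This is the only contrast that addresses rehabilitation against no rehabilitation. A conclusion that certain groups need more therapy, or need only diagnostics, would rest on it.

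**Working it through.** **Passages side by side**

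| Topic | One place | Another place | Result |
|---|---|---|---|
| Type of control | Control group section: matched | Same sentence: or comparative data | Design left open |
| Eligibility | Control group section: same criteria | Eligibility criteria: one criterion dated to start of rehabilitation; abstract: controls are without rehabilitation | That one criterion cannot be applied to controls as worded; the other four can |
| Time points | Treatment effect: admission, discharge, catamnesis | Control group section: diagnostics only, no intervention | No counterpart stated in the text for admission and discharge (check Figures 1 and 2) |
| Prognostic variables | Treatment effect: subgroup analyses | Treatment effect: group comparison, none named | Subgrouping alone does not remove confounding from the overall contrast |
| Strength of claim | Background: explorative; limitations: no randomised design | Background: tests effectiveness; limitations: reliable statements | Claim exceeds the stated safeguards |

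A random intercept or slope models within-patient correlation. It does not model selection into rehabilitation. Comparing change does remove stable level differences, so bias needs the groups' trends to differ for reasons other than treatment.

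**Size, by illustration only.** The article has no effect size, SD, power or control-group size, so there is no figure to reproduce.

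Inputs: 1000 patients, from the abstract, all taken to be in rehabilitation (assumption). Controls 100 or 200 (assumption). True effect zero. Two-sided alpha 0.05; the article gives 0.05 without sidedness. Independent patients, one change score each, clustering by clinic ignored.

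*Illustration A.* A confounder differs by d SD between groups and correlates r with change, so bias b = d × r in SD of change. Assumed d of 0.5 to 1.0 and r of 0.2 to 0.4 give b from 0.5 × 0.2 = 0.10 to 1.0 × 0.4 = 0.40.

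SE = √(1/1000 + 1/n_c): 0.077 for 200 controls and 0.105 for 100. Rejection rate = Φ(b/SE − 1.96) + Φ(−b/SE − 1.96).

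| Bias (SD) | 100 controls | 200 controls |
|---|---|---|
| 0 | 5% | 5% |
| 0.10 | 16% | 25% |
| 0.20 | 48% | 73% |
| 0.40 | 97% | >99% |

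For b = 0.10 and 200 controls: 0.10/0.0775 = 1.29; Φ(−0.67) + Φ(−3.25) ≈ 0.25.

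*Illustration B.* A different mechanism: a baseline gap of g SD that regresses, with test-retest correlation ρ. Bias = g(1 − ρ); SD of change = √(2(1 − ρ)).

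| g | ρ | Bias (baseline SD) | 100 controls | 200 controls |
|---|---|---|---|---|
| 0 | 0.5 or 0.7 | 0 | 5.0% | 5.0% |
| 0.2 | 0.5 | 0.10 | 15.9% | 25.2% |
| 0.2 | 0.7 | 0.06 | 11.4% | 17.0% |
| 0.3 | 0.5 | 0.15 | 29.8% | 49.1% |
| 0.3 | 0.7 | 0.09 | 19.8% | 32.3% |
| 0.5 | 0.5 | 0.25 | 66.4% | 89.8% |
| 0.5 | 0.7 | 0.15 | 45.5% | 70.5% |

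For g = 0.3, varying the control group from 50 to 500 and ρ over 0.5 and 0.7 gives 12.6% to 78.2%. More patients do not shrink the bias; they make it more likely to be declared significant. If the gap is stable over time, this bias is absent.

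**The case against.** The strongest reply is that this is a journal article. Lists of matching variables and covariates normally sit in a fuller document, so their absence here proves little. The study calls itself explorative, its primary questions are descriptive and need no controls, and it openly concedes that it is not randomised. Most of this stands, and it sets the limits of the point. It does not answer the stated choice between matched and unmatched controls. That is a design decision affecting recruitment, and a later analysis plan cannot fully repair it. Nor does it answer the claim of reliable treatment statements.

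Four stronger readings are tempting and are not supported:

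- **That there is no confounder control at all.** Matching is named as an option, and an analysis plan that is not shown may specify adjustment.
- **That changes are compared without any modelling.** A three-wave mixed model is specified, and it removes stable differences in level.
- **That controls cannot meet the inclusion criteria.** Four of the five apply unchanged. The fifth fails only in its timing phrase, and functional limitation could be assessed at a clinic visit.
- **That controls are selected on their later course.** One might infer this from their being without rehabilitation while everyone in Germany is entitled to it. But no rule says that controls must stay untreated until catamnesis or are dropped if they start, and the Background puts need well above capacity, so going without need not reflect recovery.

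**Conclusion.** The point holds in this form: the text leaves the only named safeguard optional, names no adjustment for the comparison, and anchors one criterion and two time points to a stay that controls do not have. Followed as written with unmatched data, it would mix any effect of rehabilitation with selection into it. The effectiveness aim and the word chosen for the strength of the conclusions then go beyond what the design supports. The descriptive primary questions are not affected.

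The reading of the text is firm; the size is not. Every bias figure above depends on an assumed confounder gap, correlation and control-group size. Nothing in the document shows that the groups' trends differ, and nothing shows that they are parallel. The direction is also open: bias could favour rehabilitation or work against it.

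**What to change.** 1. **Define one control group.** Delete the unmatched alternative. Give controls an index date as t0, date the functional-limitation criterion to it, and set t1 and t2 at intervals matching those of the rehabilitation patients. Keep controls in their group if they later start rehabilitation, with a sensitivity analysis using the catamnesis record of further medical measures.
2. **Commit to matching, or to a mixed model adjusted or weighted for variables collected at t0 in both groups:** age, sex, time since infection, number and intensity of ReCoRD symptoms, comorbidity, PHQ, FSMC and WAI. Report balance before and after. Record demographic and work data for controls directly: Data management extracts these from rehabilitation discharge letters, which controls do not have.
3. **Reword Strength and limitations** so that the comparison is reported as an association and as hypothesis-generating, and name selection into rehabilitation as a limitation.

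Cost: a few extra data items and scheduled visits for controls, analysis work, somewhat wider intervals and a more modest claim. If weighting is used, the result applies only to patients comparable across the groups, and this should be stated. Adjustment does not remove unmeasured confounding.

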## Methods/design

### Participants, interventions, and study variables

#### Study setting and recruitment

The envisaged study will take place in seven rehabilitation clinics of different specialisations: cardiological rehabilitation, pneumological rehabilitation, neurological rehabilitation, psychosomatic rehabilitation. All consecutively admitted rehabilitation patients who start rehabilitation as a result of COVID-19 and who meet the eligibility criteria as well as consent to participate in the study will be included. The previous course of infection of the affected persons is irrelevant for the inclusion in the study (e.g. mild symptoms to severe course with hospitalisation) (Fig. 1).

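### The rehabilitation-versus-outpatient contrast is a non-randomised change-score comparison with no stated control of case mix and an unsettled control group, so case-mix differences can appear as a treatment effect

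*Protocol article*

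**What the plan says.** The abstract describes the design: "This prospective, non-randomised, controlled longitudinal study, plus multi-group comparisons will take place in seven rehabilitation clinics of different specialisations". On the comparator it says: "Patients of the post-COVID outpatient clinic without rehabilitation will be used as a control group".

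The section *Treatment effect* defines the contrast as "Differences in the change scores between the intervention groups (reha-clinics) and the control group (post-COVID ambulance", to be analysed by multilevel linear regression over admission, discharge and 6-month follow-up. It specifies a random intercept, random slopes to be tested for fit, and a 0.05 threshold. Symptom severity, duration and number, and comorbidity appear there once, as subgroup variables for finding out who benefits most.

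The section *Control group* says: "This is a matched control group or comparative data from Regensburg Post-COVID Outpatient Clinic". It names no matching variable. It adds that these patients "meet the same inclusion criteria as the study cohorts of the rehabilitation clinics and receive the same diagnostic examinations", and that the outpatient setting is diagnostic only.

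The second item under *Eligibility criteria* requires "at the time of the start of rehabilitation, the presence of functional limitations that may threaten the ability to work". Under *Study setting and recruitment*, severity of the acute illness is left open: "The previous course of infection of the affected persons is irrelevant for the inclusion in the study".

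The *Background* says that the study tests whether rehabilitation is effective and safe. *Strength and limitations* concedes that the lack of randomisation is a relevant weakness, yet expects reliable statements on which therapy, and how much, patient groups need.

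**The concern.** Patients enter rehabilitation through a selection process, and *Interventions* says they are directed to clinics by symptom focus. Controls come to one outpatient clinic for diagnosis. The two groups may differ at t0 in time since infection, severity, comorbidity and work status, and each of these can influence how a patient changes over six months without any treatment.

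A change score or a random intercept removes a stable difference in level between groups. It does not remove a difference in natural course, or differential regression to the mean. The prognostic factors that the plan does name are given a different role: a subgroup analysis asks where the contrast is larger and does not make the groups comparable.

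At stake is the inference drawn from this contrast: whether rehabilitation works, and whether diagnosis alone suffices for some patients. A larger sample does not help, because it narrows the interval around a biased value.

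**Working it through.** **1. The comparability assurances, side by side**

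- Matching: the control section offers either a matched group or comparative data. These are different designs, and only the first balances anything. The choice affects how controls are selected, so it cannot safely wait for the analysis.
- Same criteria: controls are said to meet the same inclusion criteria, but the functional criterion is dated to the start of rehabilitation, and controls are patients without rehabilitation. As worded, it has no date at which it can be checked for them.
- Time since infection: eligibility sets only a lower bound (complaints persisting beyond 12 weeks), so its distribution can differ between groups.
- Analysis: the *Treatment effect* section mentions no covariate, weight or matched-set term.

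**2. Is there a figure in the article to reproduce?** No. "Within 12 months, 1000 cases across all participating centres will be included" is the only sample-size statement. No effect size, SD, power or control number is given, and it is not said whether controls are among the 1000.

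**3. Illustration of size (all inputs are assumptions except the 1000 and the 0.05 level)**

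Assume no true effect, a standardised outcome, rehabilitation patients d SD worse at t0, retest correlation r, both groups regressing to a common mean, one follow-up visit, and a two-sided test.

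- Spurious difference in change = d(1 − r). With r = 0.6: 0.3 × 0.4 = 0.12 SD; 0.5 × 0.4 = 0.20 SD.
- SD of change = √(2(1 − r)) = √0.8 = 0.894.
- SE with 1000 rehabilitation patients and 200 controls = 0.894 × √(1/1000 + 1/200) = 0.069.
- Chance of p < 0.05 ≈ Φ(bias/SE − 1.96).

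| Controls (with 1000 rehabilitation patients) | d = 0.3 | d = 0.5 |
|---|---|---|
| 100 | 25% | 57% |
| 200 | 41% | 82% |
| 300 | 53% | 92% |

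Reading the 1000 as the total, with 100, 200 or 500 of them controls, and letting d run from 0.2 to 0.5 and r from 0.5 to 0.7, the spurious difference runs from 0.06 to 0.25 SD and the false-positive rate from 11% to 98%. A simulation of one case (d = 0.3, r = 0.6, 800 versus 200, 2000 runs) rejected in 40% of runs on raw change and in 5.3% after adjustment for the t0 outcome.

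**4. The opposite assumption**

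Now suppose each group has its own stable mean, still d apart, with no true effect. The expected difference in change is d − d = 0, so the raw change score is unbiased. Adjusting for the t0 outcome then gives d − r·d = d(1 − r), again 0.12 to 0.20 SD for d = 0.3 to 0.5 at r = 0.6, now to the disadvantage of the rehabilitation group. The data cannot settle which assumption holds (Lord's paradox). Step 3 therefore shows that the bias can matter. It does not show how large it is here, or that baseline adjustment removes it.

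**The case against.** The strongest reply is that this is a condensed article. The *Treatment effect* section lists no fixed effects and never says that the model is unadjusted, so covariates and matching variables may stand in a document not shown. That is fair, and a missing covariate list is not the point here. What stands is in the printed text: a comparator defined by an either/or, a criterion that cannot be dated for one group, prognostic factors assigned to subgroups, and a non-randomised contrast headed as a treatment effect.

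Second, the study calls itself explorative, and none of its numbered research questions is rehabilitation versus control. The primary ones are descriptive, and the secondary ones concern change during rehabilitation and differences between settings. This limits the reach of the point. The *Background* and *Strength and limitations* nevertheless claim effectiveness and reliable statements on therapy need.

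Third, the numbers are assumed, and the common-mean assumption generates them. That stands in full, as step 4 of the working shows.

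A reader might also infer more than the article supports:

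- That the controls are historical. Nothing says so; the study is called prospective and the controls receive the same examinations.
- That one pooled control set will be matched to the whole rehabilitation cohort. This is not stated.
- That the 5–10% and 85% in the *Background* show acute severity driving recovery. Those are incidences of the syndrome, and every participant already has it.
- That controls lack work-threatening limitations. The article says that they meet the criteria; the fault is in the wording of the criterion.

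**Conclusion.** The point holds in a limited form. As printed, the plan settles neither who the controls are nor how the groups will be made comparable, and one criterion does not apply to controls as worded. Case-mix differences can therefore show up as a treatment effect that the stated model cannot separate from a real one.

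It would go too far to say that this will happen, or in which direction. Both depend on the baseline gap, the correlation, the control number and the natural course in each group, none of which the article gives. The percentages above are illustrative only.

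The consequence is confined to the rehabilitation-versus-control contrast and the claims built on it. The descriptive primary questions are untouched.

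**What to change.** - *Control group*: commit to one definition, matched or unmatched. If matched, name the variables.
- *Eligibility criteria*: word the functional criterion as present at t0, and say what t0 is for an outpatient, since the article defines it as admission.
- *Treatment effect*: adjust or propensity-weight each rehabilitation-versus-control contrast for t0 variables: age, sex, time since infection (with a visit interaction), acute hospitalisation, ReCoRD symptom number and intensity, comorbidity, and work status. Report balance, and the overlap between groups.
- Show each contrast both with and without adjustment for the t0 value of the outcome, because the choice rests on an untestable assumption.
- In *Treatment effect* and *Strength and limitations*, describe the estimate as an adjusted association with possible residual confounding.

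Most of these variables are already planned through ReCoRD, the WAI and the discharge letters. Controls have no rehabilitation discharge letter, so their work-status items must come from the WAI or be asked directly. The price is somewhat wider intervals and a conclusion limited to patients who have comparable controls.
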